#### Process evaluation measures

##### Acceptability questionnaire

In the penultimate week of the core programme (week-16), participants will be asked to complete a questionnaire, which assesses the acceptability of the overall programme and each component using a 5-point Likert scale. Participants will be asked about the perceived helpfulness of the overall programme to promote weight loss, the perceived helpfulness of each component, and how much effort was associated with each component.

##### Fidelity assessment

We will assess whether the intervention components are delivered as planned by collecting the following measures during the trial period:Number of participants attending the health coach introductory callDuration of the health coach introductory call for each participantNumber of participants attending the coaching drop-in sessions each weekTotal number of coaching drop-in session sessions attended per participant, out of a maximum of 17 sessionsNumber of goal setting statements completed per participant, out of a maximum of 16Number of reflection statements completed per participant out of a maximum of 16Number of food diaries completed per participant out of a maximum of 17Number of participant food diaries reviewed by the health coach at each timepoint that the food diary review is offered (weeks 4, 7, and 11)

### Sample size

The available resource allocated to this trial was 48 groups with an average of 30 participants per group. Considering the resource management principle of MOST [7], and given this allocated sample size, we calculated the available power to detect different effect sizes using the R macro %FactorialPowerPlan (Table 5).

**Table 5 Tab5:** Power calculations

**Cohen’s *****d***** effect size**	**Difference in weight**	**Power**
0.25	1 kg	92%
0.22	0.88 kg	85%
0.188	0.75 kg	75%

Power for this study is based on weight change from baseline to 16 weeks. Specifically, the study aims to assess which intervention components contribute to a more than minimal improvement in weight loss to identify components for inclusion in the optimised intervention. Our definition of at least a minimal difference in weight loss is ≥ 0.75 kg—alone or in combination with other components—at 16 weeks. We assumed a standard deviation of 4 kg from previous studies [26], which translates to a component effect size of *d* = 0.188. From a decision-priority perspective, this optimisation trial aims to screen components for an optimised intervention that could be tested in a future definitive evaluation [7, 27]. Therefore, the criteria to consider an effect important will be set liberally at *p*< .10, which is not uncommon for this phase of MOST methodology [8].

Based on previous studies, we assumed a 50% retention rate (an average of 15 participants per group) [26] and a cluster size standard deviation of 5 participants, an intraclass correlation of 0.01 and set alpha to 0.1. This sample size provides 75% power to detect a 0.75 kg difference in weight loss and 92% power to detect any differences of 1 kg or larger. Therefore, this study is powered to detect any main effects or interactions of these sizes or larger.

### Statistical Analysis

Descriptive statistics will be used to summarise the demographic characteristics of the sample.

#### Primary objective

Data will be analysed using a linear mixed-effect model with repeated measures, to assess whether each component is associated with weight change across the time points (4, 16, and 24 weeks). Participant ID will be added as a random effect, time and component as fixed effects, and an interaction term of component by time. We will also assess two-way interactions between components by adding appropriate multiplicative interaction terms.

The sensitivity of the analysis to assumptions about missing data will be assessed using appropriate methodology that could include (1) last observation carried forward, (2) baseline observation carried forward, and (3) completer analysis. Planned subgroup analyses will categorise participants into three subgroups based on their baseline BMI: (1) participants with a BMI of 21–25 kg/m^2^, (2) participants with overweight (BMI 25–30 kg/m^2^), and (3) participants with obesity (BMI > 30 kg/m^2^). We will also conduct subgroup analyses by age (based on the median age), sex, tertiles of the index of multiple deprivation (with cut points determined from the study population), and presence of pre-diabetes or type 2 diabetes at baseline.

The decision about which components to select for the optimised intervention (i.e., an intervention that includes only active components) will be based on the main effect and interaction estimates obtained from the primary analysis.

Significance levels will be set at *p* ≤ 0.10. Effect sizes and 90% confidence intervals will be reported for all analyses, given the alpha of 0.10. We will also report the more widely used 95% confidence intervals.

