### Randomisation

Participants will be allocated to closed groups in which they will undergo the programme. Allocation occurs through an algorithm which assigns participants to groups based on age and sex. Groups consist of male only, female only, and mixed sex groups plus mostly older, mostly younger, and mixed age groups. Only groups that have between 28 and 32 participants will be included in the trial, to ensure a similar number of participants will be included in each experimental condition. Groups in which the number of participants falls outside this range will continue to the standard Second Nature programme. Each eligible group will be cluster randomised to one of 16 experimental conditions. The research team will use computerised randomisation software (MinimPy version 2) to randomly allocate the groups with a minimisation algorithm to balance sex and age across the experimental conditions as much as possible. Randomisation will be performed by a researcher who will not be delivering the intervention and who does not have visibility of the screening process or the allocation of groups.

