### Outcomes and measures

Outcomes and measures are presented in Table 4.

**Table 4 Tab4:** Summary of outcomes and measures

**Outcome**	**Outcome measures**
Primary	• Weight change between baseline and 16 weeks
Secondary	• Weight change between baseline and 24 weeks • Drop-out of programme between baseline and 16 weeks • Drop-out of programme between baseline and 24 weeks • Engagement with the programme between baseline and 16 weeks • Engagement with the programme between baseline and 24 weeks
Exploratory	• Weight change between baseline and 4 weeks • Drop-out of programme between baseline and 4 weeks • Engagement with programme between baseline and 4 weeks

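### Outcome, power and selection threshold are at week 16, but the primary model targets change across weeks 4, 16 and 24 and names participant as its only random effect

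*Protocol article*

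**What the plan says.** Week 16 is fixed in three places. Table 4 (Outcomes and measures) gives the primary outcome as "Weight change between baseline and 16 weeks", with week 24 secondary and week 4 exploratory. The Sample size section says "Power for this study is based on weight change from baseline to 16 weeks". It sets the threshold for selection at the same visit: "Our definition of at least a minimal difference in weight loss is ≥ 0.75 kg—alone or in combination with other components—at 16 weeks".

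The Primary objective paragraph of Statistical Analysis describes one linear mixed model for repeated measures, used "to assess whether each component is associated with weight change across the time points (4, 16, and 24 weeks". Its structure is: "Participant ID will be added as a random effect, time and component as fixed effects, and an interaction term of component by time". Interactions between components follow in a separate sentence: "We will also assess two-way interactions between components by adding appropriate multiplicative interaction terms". The choice of components "will be based on the main effect and interaction estimates obtained from the primary analysis". No visit is attached to those estimates.

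Under Randomisation: "Each eligible group will be cluster randomised to one of 16 experimental conditions". The power calculation allows for this clustering with an intraclass correlation of 0.01. The model description has no group term.

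**The concern.** There are three linked problems.

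1. **Target.** In a model with component by time, the term called the main effect of a component is, depending on coding, either its effect at the reference visit or an average over visits. Neither is the week-16 effect unless the effect is the same at every visit. The threshold is a week-16 quantity, so a component could be kept or dropped on a number that the threshold was not set for.

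2. **Interactions.** The threshold applies to components alone or in combination, so interactions also drive selection. The products between components are described without a time term. Read that way, they may be pooled over the three visits.

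3. **Standard errors.** Groups are randomised, but participant is the only random effect named. Leaving out the group makes standard errors too small. A plain participant intercept also imposes the same variance at every visit and the same correlation between every pair of visits. Weight change from baseline need not behave like that.

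At stake is the trial's main product, the list of components carried into the optimised programme.

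**Working it through.** **Step 1. The plan's power figure is a week-16, cluster-adjusted figure.** Inputs from Sample size: 48 groups, 15 retained per group, cluster-size SD 5, intraclass correlation 0.01, SD 4 kg, alpha 0.10 (taken as two-sided). Each component level has 48 × 15 / 2 = 360 participants.

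- Design effect: 1 + ((1 + (5/15)²) × 15 − 1) × 0.01 = 1.157.
- Standard error of a component effect: 4 × √(2 × 1.157 / 360) = 0.321 kg.
- Power at 0.75 kg: Φ(0.75/0.321 − 1.645) = Φ(0.694) = 75.6% (stated 75%).
- The same formula gives 86.4% at 0.88 kg (stated 85%) and 93.0% at 1 kg (stated 92%).

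Without clustering the figures would be 80.8%, 90.4% and 95.6%, which do not match. So the power calculation counts the group, while the model as described does not.

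**Step 2. What the target does to a qualifying component.** The protocol gives no effect profile over time, so these are assumptions. All have 0.75 kg at week 16.

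| Effect at weeks 4 / 16 / 24 (kg) | Average over visits | Week-4 reference effect |
|---|---|---|
| 0.25 / 0.75 / 0.75 | 1.75/3 = 0.58 | 0.25 |
| 0.20 / 0.75 / 0.90 | 1.85/3 = 0.62 | 0.20 |
| 0.30 / 0.75 / 0.50 | 1.55/3 = 0.52 | 0.30 |
| 0.40 / 0.75 / 1.00 | 2.15/3 = 0.72 | 0.40 |
| 0.75 / 0.75 / 0.75 | 0.75 | 0.75 |

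The average falls below 0.75 kg whenever the week-4 and week-24 effects add to less than 1.5 kg, and exceeds it when they add to more. With component by time in the model and the first profile, a simulation recovered the week-16 effect as 0.750 kg and the average as 0.583 kg. The right number is therefore available if it is named.

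**Step 3. Omitting the group.** The true level of an unadjusted nominal 10% test is 2(1 − Φ(1.645/√DE)). With DE = 1.157, 1.645/1.0755 = 1.530 and the level is 12.6%. Standard errors are 1/1.0755 = 0.93 of their proper size. For other intraclass correlations at 15 per group, the level is 11.3% (0.005), 15.1% (0.02) and 21.8% (0.05).

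**Step 4. A plain participant intercept, with clustering set aside.** The protocol gives one SD (4 kg) and one retention rate (50%); I take both as the week-16 values. SDs and availability at weeks 4 and 24 are assumed, as are correlations of 0.6 (weeks 4 and 16), 0.5 (4 and 24) and 0.85 (16 and 24). With equal availability, the ratio of model to true standard error at week 16 is r = √(mean of the three variances)/4. For SDs 3/4/6 that is √((9 + 16 + 36)/3)/4 = 4.509/4 = 1.13. With monotone dropout, r compares the model-based and robust large-sample variances of the best-fitting random-intercept model. The true level is 2(1 − Φ(1.645 r)).

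| SD at weeks 4/16/24 (kg) | Weights available | r | True level |
|---|---|---|---|
| 2 / 4 / 4.5 | 75 / 50 / 42% | 0.82 | 17.6% |
| 3 / 4 / 5 | 75 / 50 / 42% | 0.95 | 11.9% |
| 3 / 4 / 5 | 60 / 50 / 45% | 0.98 | 10.6% |
| 3 / 4 / 5 | equal | 1.02 | 9.3% |
| 3 / 4 / 6 | 75 / 50 / 42% | 1.04 | 8.8% |
| 2 / 4 / 6 | equal | 1.08 | 7.6% |
| 3 / 4 / 6 | equal | 1.13 | 6.4% |

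The direction depends on figures the protocol does not give.

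**Step 5. Both together, one assumed case.** I took 48 groups of 30, intraclass correlation 0.01, SDs 2/4/5 kg, correlations 0.7, 0.6 and 0.9, weights available in 70/50/40%, and a participant intercept only. In 1,500 simulated trials with no effect, the week-16 contrast had a model standard error of 0.246 against a true 0.309 and rejected in 17.9%. The time average had 0.201 against 0.264 and rejected in 20.5%.

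**The case against.** The best defence is that the article already points to week 16. Table 4 makes it primary, the threshold is stated at week 16, and one model over three visits is an economical way to serve the secondary and exploratory outcomes too. On that view, primary analysis simply means the week-16 contrast, and residual covariance and contrast coding belong in an analysis plan that is not shown.

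Much of this stands. Silence on the residual covariance is not a fault in itself, and the intended reading may well be week 16. But the paragraph does more than stay silent: it states a target across visits, a random effect and a basis for selection, and none of these is tied to week 16 or to the randomised group.

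Some stronger readings do not stand:

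- A reader might infer that the selection estimates will be diluted. The component-by-time term makes the week-16 effect estimable, so dilution needs a particular choice of estimate and an effect that changes over time.
- A reader might infer that interactions are certainly averaged over visits. The text asks only for appropriate product terms and does not exclude their crossing with time.
- A reader might expect a small week-4 effect because little has been delivered by then. The protocol places the introductory call in the first two weeks and offers drop-in sessions weekly in the first month. A smaller effect at week 4 remains plausible because weight loss accrues, but the profile is an assumption.

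**Conclusion.** The mismatch is real and worth correcting. Outcome, power and threshold are at week 16; the stated model target and the estimates used for selection are not tied to that visit.

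- **Selection.** Under assumed profiles with a true 0.75 kg at week 16, a time average reads 0.52 to 0.72 kg and a week-4 reference effect 0.20 to 0.40 kg. With a constant effect there is no loss.
- **Group term.** This is the firmest of the error-rate results. On the protocol's own inputs, leaving the group out turns a 10% test into about 12.6%.
- **Participant intercept.** A reader might infer that it always understates the week-16 standard error. The protocol gives no SDs or availability by visit, and over the assumed scenarios the ratio runs from 0.82 to 1.13, with a true level of about 6% to 18%. It is a risk in either direction, not a demonstrated bias. The 17.9% and 20.5% in step 5 include clustering and should not be attributed to the covariance alone.

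**What to change.** Name the week-16 component contrasts, and the week-16 two-way interaction contrasts, as the primary estimates and the sole basis for selection. Take them from a model with:

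- time as categorical;
- component-by-time and component-by-component-by-time terms;
- an unstructured within-participant covariance over the three visits;
- a random effect for the randomised group.

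Report the week-24 and week-4 contrasts as the secondary and exploratory results already listed in Table 4.

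The cost is wording and a few parameters. The covariance has six parameters instead of two. Crossing the six two-way interactions with three visits adds 6 × 2 = 12 fixed effects. Within the scenarios of step 4, the unstructured week-16 standard error was never larger than the random-intercept model's true one (for example 0.280 against 0.285 kg). The group term widens intervals by about 7.6% at the stated inputs (√1.157 = 1.076), which the power calculation already allows for.

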#### Secondary objectives

For the secondary outcome, the proportion of participants that drop-out from baseline to 4, 16, and 24 weeks will be assessed using logistic regression analyses.

We will also explore whether engagement acts as a mediator in the association between components and weight change. Mediation effects will also be tested for significance using the general approach described previously [28]. Engagement will be considered as a mediator if engagement significantly predicts weight and if the group effect is attenuated with adjustment for the engagement variable. The indirect effect and proportion of total effect mediated will also be calculated.

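### The primary mixed model has no term for the randomised group, so its standard errors are about 7% too small at the plan's own ICC

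*Protocol article*

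**What the plan says.** The protocol article makes the group the unit of randomisation. Its Randomisation section says: "Each eligible group will be cluster randomised to one of 16 experimental conditions". Under Core intervention, group members share a chat and a health coach. Under Randomisation, groups are formed by age and sex.

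The Sample size section plans for this. It starts from the resource: "The available resource allocated to this trial was 48 groups with an average of 30 participants per group". It then assumes 50% retention, which leaves an average of 15 per group, with "a cluster size standard deviation of 5 participants, an intraclass correlation of 0.01 and set alpha to 0.1". The resulting powers for component effects of 0.75, 0.88 and 1 kg are 75%, 85% and 92%.

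The Primary objective part of Statistical Analysis then lists the model terms: "Participant ID will be added as a random effect, time and component as fixed effects, and an interaction term of component by time". Two-way component interactions are added. Nothing in the article mentions a random effect for group, cluster-robust errors, generalised estimating equations (GEE) or a cluster-level analysis. The reference to a group effect under Secondary objectives concerns the component effect in the mediation model.

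For drop-out, the Secondary objectives part says only that the proportions "will be assessed using logistic regression analyses" and lists no terms.

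**The concern.** In a cluster-randomised trial, the component contrast varies through differences between groups as well as between people. If the model's only random effect is the participant, two members of one group are treated as independent once their components are known. With any positive ICC, which the plan itself assumes, the model-based standard errors of the component effects are then too small.

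This bears on the trial's main decision. The Sample size and Statistical Analysis sections judge effects at a p-value of 0.10. They also base the choice of components on the main-effect and interaction estimates from this model, and 90% and 95% intervals are to be reported from it. The 10% level is already liberal on purpose, so an unacknowledged further increase should not be added to it.

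**Working it through.** **Inputs, all from the Sample size section:** 48 groups; mean 15 analysed per group, so N = 48 × 15 = 720, or 360 per level of each component; cluster size SD 5, so coefficient of variation CV = 5/15 = 0.333; ICC 0.01; SD of weight change 4 kg; alpha 0.10. Sidedness is not stated; two-sided reproduces the table.

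**Step 1. Design effect.** DE = 1 + [(1 + CV²) × 15 − 1] × ICC = 1 + (1.111 × 15 − 1) × 0.01 = 1.157. Its square root is 1.075.

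**Step 2. Standard error of a component main effect.**
- Ignoring the group: 4 × √(2/360) = 0.298 kg.
- Allowing for it: 0.298 × 1.075 = 0.321 kg.
- Ratio 1/1.075 = 0.930, so the unadjusted standard error is about 7% too small.

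**Step 3. Reproduce the power table.** Power = Φ(difference/SE − 1.645).

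| Difference | Stated | With DE 1.157 | Clustering ignored |
|---|---|---|---|
| 0.75 kg | 75% | 75.6% | 80.8% |
| 0.88 kg | 85% | 86.4% | 90.4% |
| 1 kg | 92% | 93.0% | 95.6% |

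A t reference with 32 degrees of freedom and the same design effect gives 74% / 85% / 92%. The table therefore matches a cluster-adjusted test and does not match an unadjusted one.

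**Step 4. Error rate of the model as written.** Under no effect, the unadjusted statistic has a standard deviation of about 1.075, so the two-sided error is 2 × [1 − Φ(1.645/1.075)] = 12.6% at the nominal 10%. At the nominal 5% it is 6.8%. Coverage of the 90% and 95% intervals is thus about 87.4% and 93.2%. A simulation with one weight change per person in 48 groups also gave 12.6%, against 10.25% for a cluster-level analysis.

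**Step 5. Sensitivity to the ICC.** Only 0.01 stands in the plan; the other values are assumptions.

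| ICC | DE | Error at nominal 10% |
|---|---|---|
| 0.01 (plan) | 1.157 | 12.6% |
| 0.02 (assumed) | 1.313 | 15.1% |
| 0.03 (assumed) | 1.470 | 17.5% |
| 0.05 (assumed) | 1.783 | 21.8% |

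**Step 6. What this does to selection.** The smallest estimate reaching p = 0.10 is 1.645 × 0.298 = 0.49 kg without the group and 1.645 × 0.321 = 0.53 kg with it. At an assumed ICC of 0.05 it is 1.645 × 0.298 × √1.783 = 0.65 kg (normal approximation). All of these lie below the 0.75 kg threshold.

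**The case against.** The strongest reply is that the practical effect is small. The trial is a deliberately liberal screen, and the Abstract and Sample size section define a worthwhile improvement as at least 0.75 kg. That threshold exceeds the significance boundary with or without the group term. If it is applied to the main-effect estimate, the selected components will hardly change. This stands, and it limits the consequence. It does not rescue the model: the Sample size section also names p < .10 as the criterion for an important effect, and the intervals are reported whichever rule decides.

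Some stronger readings are tempting but not supported:

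- **Inactive components entering the package more than 10% of the time.** The 12.6% is two-sided, and a component that appears to reduce weight loss would not be chosen. On the p-value alone, wrongful inclusion is about 12.6%/2 = 6.3% against 5%.
- **A higher error rate from a t reference with few degrees of freedom.** That reference belongs to the corrected test. The unadjusted standard error rests on hundreds of participants, so the normal calculation applies.
- **A drop-out model that leaves out the group.** The article lists no terms for that model, not even the components. Silence there is not a decision, and the detail may stand in a fuller document. The same holds for the mediation and subgroup models. The documents also give no ICC for drop-out.
- **Error rates near 20%.** These need an ICC that the plan does not state.

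An unseen analysis plan might contain the group term. But the article lists the primary model's random effect rather than leaving it open, so this is a stated model that conflicts with the design, not an omitted detail.

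**Conclusion.** Wrong as written for the primary model. The group is randomised and enters the power calculation, but it is absent from the listed model terms. At the plan's own ICC of 0.01, the component standard errors are about 7% too small and the nominal two-sided 10% test has about 12.6% error.

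The size rests on the plan's figures for group size and ICC. It also treats the analysis as one 16-week value per person, whereas the stated model takes weeks 4, 16 and 24 together, so the numbers contributing and the design effect will differ somewhat. The direction is certain for any positive ICC. The understatement is modest at 0.01 and larger if the true ICC is higher. For drop-out, mediation and subgroups, the point is only that the article should say that the group will be accounted for.

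**What to change.** In the Primary objective text, add a random intercept for the randomised group, with participant nested in group, and use a small-sample degrees-of-freedom correction suited to 48 groups (Kenward-Roger or Satterthwaite would serve).

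Under Secondary objectives, state that the drop-out analysis will account for the group, by a mixed logistic model or GEE with a small-sample correction. Carry the same clustering into the mediation and subgroup models.

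This costs a wording change and one extra term per model, with no new data and no change to trial conduct. Intervals become slightly wider: about 7.5% at the plan's ICC (0.321/0.298), plus a little for the degrees of freedom. Planned power is not reduced, because Table 5 already assumes the adjustment.

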### Screening, consent, and baseline assessment

Eligibility criteria will be assessed, and baseline data collected, via Second Nature’s bespoke self-reported health questionnaire which will be completed as part of the sign-up process on the Second Nature website prior to commencement of the programme, with no additional instruction. During the questionnaire, participants will be asked to self-report demographic characteristics (date of birth, and sex), anthropometric measures (body weight and height), health-related conditions (diabetes, physical, and mental health conditions), current pregnancy, and their main priorities and goals for the programme. If the participant is ineligible, a pop-up will explain that they do not meet the eligibility criteria for the Second Nature programme, they will not be able to proceed further, and no identifiable information will be collected.

Participants who meet the eligibility criteria will be able to review and accept the Second Nature Terms & Conditions and Privacy Policy, which involves providing consent to be involved in internal and external research and for their data to be used for academic research purposes (Supplementary Material 2). They will then be able to complete the sign-up process, where they can purchase the programme and input their personal contact details (name, email, and home postcode). After sign-up, participants will receive instructions on how to download the Second Nature app. After downloading the app, participants will also be asked to weigh themselves using their weighing scales and record their baseline weight reading in the app.

Participants have the right to withdraw from the programme, and hence also from the trial, and request that all data that has been collected on them is deleted, with no obligation to give a reason.

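### The primary weight model lists no baseline weight and neither of the minimisation factors (sex, age): precision is given up that adjustment would recover almost free

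*Protocol article*

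**What the plan says.** The primary outcome in Table 4 (Outcomes and measures) is "Weight change between baseline and 16 weeks", in kilograms. Under Statistical Analysis, Primary objective, the analysis is set out in three steps: "Data will be analysed using a linear mixed-effect model with repeated measures"; then a random effect for participant, with "time and component as fixed effects, and an interaction term of component by time"; then "We will also assess two-way interactions between components by adding appropriate multiplicative interaction terms". No covariate is named there or elsewhere in the article. Age, sex and baseline BMI return only as subgroup variables.

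The Randomisation section describes how the clusters are built: "Groups consist of male only, female only, and mixed sex groups plus mostly older, mostly younger, and mixed age groups". They are then allocated "with a minimisation algorithm to balance sex and age across the experimental conditions as much as possible". Weight and BMI are not minimisation factors.

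The variables are all to hand. Date of birth, sex, weight and height come from the sign-up questionnaire, and participants are later asked to "record their baseline weight reading in the app" (Screening, consent, and baseline assessment). Table 2 sets a lower BMI bound of 21 and no upper bound.

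**The concern.** Design and analysis do not match. The design treats sex and age as worth balancing and sorts participants so that much of the variation in both lies between groups. The model then ignores both. When balancing factors are left out, the variation they explain stays in the residual although the allocation has already removed part of it from the treatment contrast. Taken alone, this tends to make standard errors too large.

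Baseline weight is in a different position: it is neither balanced nor adjusted for. Taking change from baseline subtracts the starting value but does not remove its relation with kilograms lost, since heavier people can be expected to lose more in absolute terms. The assumed 50% retention adds to this, because balance at randomisation need not carry over to those analysed.

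What is at stake is precision at the selection threshold. Components are chosen on the main effect and interaction estimates, the smallest difference of interest is 0.75 kg, the article itself gives 75% power for it, and the sample is fixed by resource. Adjustment is one of the few ways left to sharpen the estimates.

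**Working it through.** **Inputs from the Sample size section.** 48 groups; 15 analysed per group (50% of 30), so N = 720; cluster-size SD 5, so CV = 5/15 = 0.333; ICC 0.01; SD 4 kg; alpha 0.10, taken as two-sided because it is paired with 90% intervals.

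**Step 1: reproduce the stated power without covariates.**
- Design effect = 1 + ((1 + CV²) × 15 − 1) × ICC = 1 + (1.111 × 15 − 1) × 0.01 = 1.157.
- Each main effect compares 24 with 24 groups if allocation is balanced, so SE = 2 × 4 × √(1.157/720) = 0.321 kg.
- Degrees of freedom = 48 groups − 11 group-level parameters (intercept, 4 main effects, 6 two-way interactions) = 37.
- Non-central t power with 37 df: 74.3% for 0.75 kg, 85.3% for 0.88 kg, 92.2% for 1 kg. The normal approximation gives 75.6%, 86.4% and 93.0%.
- Table 5 states 75%, 85% and 92%. These figures reproduce with the full SD of 4 kg, so no covariate gain is built in and the stated power is consistent with an unadjusted analysis.

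**Step 2: add covariates.** Let r be the multiple correlation of baseline weight, age and sex with 16-week change. It is not in the documents, so 0.2 to 0.4 is an assumed range. The SE is multiplied by √(1 − r²), and the equivalent gain in sample size is 1/(1 − r²) − 1.

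| r | variance removed | SE (kg) | power for 0.75 kg, 37 df | equivalent extra participants |
|---|---|---|---|---|
| 0 | 0% | 0.321 | 74.3% | none |
| 0.2 | 4% | 0.314 | 75.8% | 4% |
| 0.3 | 9% | 0.306 | 77.7% | 10% |
| 0.4 | 16% | 0.294 | 80.5% | 19% |

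**Step 3: charge the degrees of freedom.** If the sex and age group factors have three levels each (an assumption from the group types listed), they use 4 df, leaving 33. Power for 0.75 kg is then 75.6%, 77.5% and 80.4% at r = 0.2, 0.3 and 0.4. At r = 0.1 it is 74.5%, a net gain of about 0.2 points.

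**Step 4: chance imbalance in baseline weight.** All inputs here are assumed: baseline weight SD 15-20 kg, between-group ICC of baseline weight 0.05-0.30, slope 0.03-0.08 kg lost per kg of starting weight.
- Low end: design effect 1 + (16.67 − 1) × 0.05 = 1.783; SE of the imbalance = 2 × 15 × √(1.783/720) = 1.5 kg; shift in the main effect = 1.5 × 0.03 = about 0.05 kg.
- High end: design effect 1 + 15.67 × 0.30 = 5.70; SE of the imbalance = 2 × 20 × √(5.70/720) = 3.6 kg; shift = 3.56 × 0.08 = about 0.28 kg.

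A one-standard-error imbalance therefore moves a main effect by about 0.05-0.28 kg, against a sampling SE of 0.32 kg and a threshold of 0.75 kg.

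**The case against.** The strongest reply is that a journal article condenses. The model is described in a few lines, nothing says it is unadjusted, and an analysis plan that is not shown may list covariates. This stands in part: their absence from the full plan is not proven. But the article names random and fixed effects one by one and bases component selection on that analysis, so a reader will take the list as complete.

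The second reply is that the benefit is small and rests on an assumed correlation. That stands. At r = 0.2 the gain is about 1.5 points, no more than the difference between the normal and t calculations. Only r near 0.4 reaches 80%.

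Third, several stronger readings are tempting, and the documents do not support them:
- A reader might infer that imbalance among about three groups per condition feeds directly into the results. Main effects and two-way interactions use all 48 groups, and no comparison of single conditions is planned.
- A reader might infer that sex and age imbalance distorts the estimates. The minimisation already limits it at randomisation. For these two factors, what mainly remains is standard errors that do not reflect the balancing.
- A reader might infer that the listed analysis is conservative overall. That is not established. The listed model also has no random effect for group, a separate point that can push the error rate the other way.
- A reader might infer bias. Chance imbalance in baseline weight is not bias in expectation.

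**Conclusion.** The point holds as an efficiency recommendation. As written, the primary model omits both minimisation factors and baseline weight, although all are recorded before the programme starts. The article's power figures are not in error; they describe an unadjusted analysis correctly.

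On an assumed correlation of 0.2 to 0.4, adjustment lifts power for 0.75 kg from about 74% to about 76-80%, equivalent to 4-19% more participants. Below r = 0.2 the gain is negligible. These calculations presume an analysis that respects the clustering, which the listed terms do not by themselves provide. Confidence is high that the terms are missing from the article and that adding them is the better method. It is only moderate about the size of the gain. Baseline weight is the most important of the three, because nothing in the design balances it.

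**What to change.** In Statistical Analysis, Primary objective, prespecify these as fixed effects in the primary weight model:
- individual baseline weight, using the same reading from which change is calculated, with a baseline-by-time interaction because the model spans 4, 16 and 24 weeks;
- individual age and sex;
- the group-level sex and age factors, coded as they were entered in the minimisation. The article does not give that coding, so it should be stated.

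Report the model without these covariates as a sensitivity analysis. Settle this before the data are transferred, so that the choice between adjusted and unadjusted results cannot depend on the results. Using the same terms in the drop-out and engagement analyses is optional.

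The cost is a change of wording and a few group-level degrees of freedom (37 to 33 if each factor has three levels, which costs about 0.2 points of power for 0.75 kg). No new data are needed. Covariate adjustment does not replace a random effect for group, which has to be dealt with separately.
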